### Control group

No intervention liable to affect reception of patients, the organization of care or the practices of health care professionals will be implemented during the Off phases. Patients will be seen based on the order of severity as assessed by the physician and based on the reason for the consultation recorded at admission.

### Outcomes and measurements

#### Primary outcome

The primary outcome is professional-reported incivilities or violence by patients, or those accompanying them, against health care staff at the OED or against other patients and/or those accompanying them. Health care professionals will be informed of the study and trained to notify any incivility or violence by a patient they may be subject to or witness.

Incivility or violence are to be described using a classification that distinguishes four levels, from least to most severe (see Table 1), based on the French National Observatory of Violence in Hospitals [9].

**Table 1 T1:** Four levels of Incivility or violence, from least to most severe

Level 1	Insistent questions, incivility, rudeness, occupation of the corridor, spitting, making noise (telephone, etc.)
Level 2	Insult or verbal abuse without threat
Level 3	Verbal abuse or physical threat
Level 4	Intentional violence, assault, vandalism or damage to equipment

#### Secondary outcomes

The secondary outcomes are

OED waiting times, measured as the period of time between the patient’s administrative check-in and the care of a physician.

The patient leave rate measured as the proportion of patients having left the OED without having received medical treatment,

Work-related stress of OED health care personnel, as measured by the Karasek questionnaire, a French validated questionnaire,

Satisfaction of patients treated at the OED.

### Sample size calculation

The number of patients has been calculated based on following hypotheses:

A 20% initial rate of incivility/violence against OED staff, whatever the severity of the violence,

A minimum 2.5% reduction in incivility/violence with each new intervention A to E,

An average of 62 patients per day expected,

The independence of the 5 interventions,

A risk alpha of 5% and the statistical power of 80%.

The statistical unit is the patient admitted to the OED. Using the Casagrande and Pike method [23], and based on the aforementioned hypotheses, the sample size required is 30,224 patients for the 5 alternating intervention phases (see Table 2).

**Table 2 T2:** Sample size required by intervention phase

**Interventions**	**TControl**	**TIntervention**	**Sample size required**
Intervention A	20%	17,5%	7802
Intervention B	17,5%	15%	6986
Intervention C	15%	12,5%	6108
Intervention D	12,5%	10%	5166
Intervention E	10%	7,5%	4162

Note:

TControl is the rate of incivility/violence in the control group (Off).

TIntervention is the rate of incivility/violence in the intervention group (On).

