**Methods/Design:**

This study is a single-center prospective, controlled time-series study with an alternate-month design. The prevention program is based on the successive implementation of five complementary interventions: a) an organizational approach with a standardized triage algorithm and patient waiting number screen, b) an environmental approach with clear signage of the premises, c) an educational approach with informational videos for patients and accompanying persons in waiting rooms, d) a human approach with a mediator in waiting rooms and e) a security approach with surveillance cameras linked to the hospital security. The primary outcome is the rate of incivility or violence by patients, or those accompanying them against healthcare staff. All patients admitted to the ophthalmological emergency department, and those accompanying them, will be enrolled. In all, 45,260 patients will be included in over a 24-month period. The unit analysis will be the patient admitted to the emergency department. Data analysis will be blinded to allocation, but due to the nature of the intervention, physicians and patients will not be blinded.

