### Time frame

The planned Inclusion period is 24 months:

“Pre-intervention” phase (phase 0) for 2 months. During this period, no specific intervention will implemented as part of the study. In all, around 3,780 patients will be enrolled over two months.

“Implementation of interventions A to E” phase (phase 1) for 20 months. In all, 37,820 patients will be enrolled.

“Simultaneous interventions A to E” phase (phase 2) for 2 months. This final observational period will enable us to compare outcome criteria before and after implementation of the prevention program. In all, around 3,780 patients will be enrolled over two months.

Furthermore, this study includes an approximately 6-month preparation and healthcare staff awareness campaign on reporting incivility and violence.

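### The 80% power per intervention assumes that the incivility rate does not vary between months; with allocation by whole months it is not assured, and two accrual figures need reconciling

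*Protocol article*

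**What the plan says.** The Sample size calculation section assumes "A 20% initial rate of incivility/violence against OED staff, whatever the severity of the violence", then "A minimum 2.5% reduction in incivility/violence with each new intervention A to E", which Table 2 applies as 2.5 percentage points at each step. With "A risk alpha of 5% and the statistical power of 80"% and the Casagrande and Pike method, it concludes that "the sample size required is 30,224 patients for the 5 alternating intervention phases": 7,802, 6,986, 6,108, 5,166 and 4,162 for A to E. The statistical unit is the patient, and 62 patients per day are expected.

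Under Study design, each intervention alternates one-month On and Off periods over four months, so a block holds two On and two Off months. Under Data analysis, On and Off rates are compared in each block with a chi-square (Khi-2) test on patients. Mixed models with random effects are described only for phase 0 versus phase 2.

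On accrual, the Time frame section says of phase 1, "In all, 37,820 patients will be enrolled", and of phases 0 and 2 alike, "In all, around 3,780 patients will be enrolled over two months". The Abstract says, "In all, 45,260 patients will be included in over a 24-month period". The Trial status section places phase 0 in January and February 2014.

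**The concern.** All patients in a month share the same On or Off status. Anything that moves the unit's rate from one month to the next (crowding, staffing, reporting habits) goes straight into the On/Off contrast, and two months per arm average out little of it. A size computed for independent patients delivers its nominal power only if that variation is zero, and the article does not state that assumption. The independence it does assume is between the five interventions, not between patients of the same month.

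What is at stake depends on the analysis. If the test allows for months, a block with no significant difference may be read as adequately powered when it was not. If the patient-level chi-square is kept, its error rate exceeds 5% and a chance difference between months may be credited to an intervention.

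Separately, block A's expected accrual is below its own requirement, and the enrolment totals disagree.

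**Working it through.** **1. Table 2.** With p₁ the Off rate, p₂ the On rate, d = p₁ − p₂ = 0.025 and p̄ their mean:

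A = [1.96√(2p̄q̄) + 0.84√(p₁q₁ + p₂q₂)]², n per arm = A[1 + √(1 + 4d/A)]² / (4d²).

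Block A (20% v 17.5%): A = 2.388, and total 2n = 7,800.8. Blocks B to E give 6,985.4, 6,107.2, 5,166.2 and 4,162.3. This is Table 2 up to rounding, two-sided, and its entries sum correctly to 30,224. No design effect is hidden in it.

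**2. Expected accrual per block.** 37,820 / 5 = 7,564 = 62 × 122 days, or 7,564 / 4 = 1,891 per month. Block A: 7,802 − 7,564 = 238 short (3.1%). The longest four-month span, 123 days, gives 7,626. Under patient independence, power for A at 7,564 is 78.7% (continuity-corrected) or 79.6% (uncorrected). B to E, corrected, have 83%, 88%, 93% and 97%.

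**3. Power with month-to-month variation.** The article gives no between-month SD, so the SDs (s) below are assumptions, held equal across blocks in percentage points.

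SE = √{[2s² + (p₁q₁ + p₂q₂)/1,891] / 2}, power = Φ(0.025/SE − 1.96).

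Block A at s = 1 point: p₁q₁ + p₂q₂ = 0.16 + 0.144375 = 0.304375. SE = √[(0.0002 + 0.000161)/2] = 0.01343, 0.025/SE = 1.861, and power = Φ(−0.099) = 46%.

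| Assumed SD (points) | A | B | C | D | E |
|---|---|---|---|---|---|
| 0 | 80% | 84% | 88% | 93% | 97% |
| 0.25 | 77% | 81% | 85% | 90% | 95% |
| 0.5 | 68% | 72% | 76% | 81% | 86% |
| 1 | 46% | 48% | 50% | 53% | 55% |
| 2 | 21% | 21% | 21% | 22% | 22% |

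These figures treat the SD as known. If it had to be estimated from the block's own four months (t-test, 2 df), power would be 35% (A) to 54% (E) even at SD 0, and about 20% to 23% at SD 1.

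For scale, an SD of 1 point in block A is an intra-month correlation of 0.0001 / (0.1875 × 0.8125) = 0.00066.

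**4. The planned chi-square under the same variation.** With no effect and a common rate p, its variance is too small by the factor 1 + 1,891s²/(pq), so the true type I error is 2[1 − Φ(1.96/√factor)]. At the Off rate:

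- SD 0.5: A factor 1.295, error 8.5%; E factor 1.525, error 11.3%.
- SD 1: A factor 2.182, error 18.4%; E factor 3.101, error 26.6%.

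Using the mean of the On and Off rates instead gives 9% to 12% and 19% to 29%.

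Under the assumed effect at SD 1, it rejects with probability Φ[(0.025 − 1.96√(p̄q̄/1,891))/SE]. For A this is Φ[(0.025 − 0.01759)/0.01343] = 71%; for E, Φ[(0.025 − 0.01274)/0.01192] = 85%.

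**5. Totals.** 3,780 + 37,820 + 3,780 = 45,380, which is 120 above 45,260. The latter is 62 × 730. If the phases run without a gap from January 2014:

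- Phase 0, January-February 2014: 59 days × 62 = 3,658.
- Phase 1, March 2014-October 2015: 610 × 62 = 37,820.
- Phase 2, November-December 2015: 61 × 62 = 3,782.

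The sum is exactly 45,260, so only the phase 0 figure is off, by about 122.

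**The case against.** The sizing and the planned test agree with each other: both take patients as independent, and Table 2 is arithmetically right. This stands, so the issue is the fit between sizing and allocation, not a calculation error.

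A reader might infer that true power is far below 80%. The documents do not support that as a fact, because they give no between-month SD. At 0.25 points B to E still exceed 80%; at 0.5 points D and E do.

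A reader might also infer that the written plan mainly risks falsely reassuring null results. Under the chi-square as written, rejection at SD 1 stays at 71% to 85% and the excess false positives are the larger problem. The lower powers apply to an analysis that respects months.

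The block A shortfall could be read as leaving A underpowered. It costs about one point, and since 62 per day is an expected average, about 64 per day (7,802 / 122) would close it. Table 2 shows each block's requirement openly, so nothing is concealed.

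The article qualifies 3,780 as approximate, and a 120-patient difference (0.3%) has no bearing on power. Both are true, but the printed totals still do not agree.

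A full analysis plan, not shown, may model months. That would not repair the power statement, since the article itself fixes the unit, formula and 80%.

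**Conclusion.** The concern holds in a conditional form. The stated 80% is correct only if the rate does not vary between months, and nothing in the article states or supports that condition. The loss ranges from slight (SD 0.25 points: A 77%, E 95%) to severe (SD 2 points: 21% and 22%), on SDs assumed here. It also rests on 1,891 patients per month, the article's own rates, and a large-sample test that treats the SD as known, which is favourable to the design. Power of 80% is therefore not assured; how far it is missed cannot be said from the document.

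If the chi-square is retained, the consequence is a type I error above 5% rather than mainly lost power. The block A shortfall and the totals are minor reconciliations.

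**What to change.** In the Sample size calculation section, replace the unconditional "the statistical power of 80"% with power per block at the expected accrual of about 7,564. Compute it under an analysis that allows for month-to-month variation, over a stated range of between-month SDs. State that block A is expected to fall slightly short of 7,802.

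In the Time frame section, correct phase 0 to about 3,658 (59 days) and keep 37,820 for phase 1 and about 3,782 for phase 2, so that the total is the 45,260 in the Abstract.

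The cost is rewording and a less favourable power statement. No extra patients and no change to the interventions are needed.

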### Blinding

Health care providers, participants and researchers will not be blinded to the intervention phase.

### Ethical approval and informed consent

Approval for the study was obtained from the hospital ethics committee, from the Sud Est III Institutional Review Board (study identifier: 2008–036 B) and from the French Data Protection Agency (CNIL).

As the promoter of this biomedical research, which falls within the scope of French Law n°2004-806 of 9 August 2004, the Hospices Civils de Lyon has acquired liability insurance coverage and stood as guarantors of the proper execution of the study.

Consent of the health care staff was sought before the study. As stipulated by French law, and given the study methodology and type of intervention, no patient consent was required [24].

### Data analysis

Data analysis will be performed by the data management and analysis center, using SAS/STAT® software. The unit of analysis will be the patient admitted to the OED. Analyses will be performed on an intent-to-treat basis.

Analyses of data from phase 1 “Implementation of interventions A to E”, will enable estimation and comparison of the average rates of violence committed against OED staff between the On and Off periods of each intervention (primary analysis). It will also enable the average rate of violence against patients, the mean rate of patients’ leaving before care, and average OED waiting time to be calculated for each intervention (secondary analyses). Finally, we will attempt to identify predictive factors for the primary outcome and secondary outcomes. Measurements of the incivility/violence rates in the intervention and controls groups will be compared for each of the 5 intervention phases using a Khi-2 test. The average waiting times in the intervention/control groups will be compared for each of the 5 interventions using a Student test.

Analyses of data from phase 0 “pre-intervention” and phase 2 “Simultaneous interventions A to E” will enable the proportion of admitted patients committing violence against medical staff to be compared before and after implementation the overall prevention program (primary analysis) and healthcare staff well-being and OED patient satisfaction to be compared.

The rate of incivility and other outcome criteria (e.g. mean waiting times, patient satisfaction, etc.) will be compared before and after implementation of the prevention program (phase 2 vs phase 0) using standard tests.

A bivariate analysis will select potential confounding factors with a view to multivariate modeling.

Modeling to compare primary and secondary outcome criteria between phase 0 and phase 2 will use nonlinear and linear mixed models (proc GLIMMIX and proc MIXED of SAS/STAT® software v9.2), taking into account confounding factors and fixed and random effects.

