### Objective

The study aims to assess the impact of a violence prevention program geared to reducing the incivilities or violence against health care workers in an ophthalmological emergency department (OED) at a teaching hospital. Our prevention program was designed in order to minimize the discomfort of patients visiting the OED.

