## Discussion

### Discussion of study design

The strengths of this study include active solicitation of event reporting, the fact that this is a prospective study and the study design enabling assessment of each intervention in the program.

In certain situations, it may be of interest to use an alternate-month study design, i.e. alternating On (intervention) and Off (control) periods which provide a series of before and after studies with interventions repeated over time [25]. This type of study design can be used only when there is no residual affect during Off periods. It is particularly well-suited to assess the impact of IT tools [26]. This design may be of particular interest when assessing the impact of an intervention in a single health care facility, which makes a randomized controlled study difficult to perform [27].

Unlike a simple before/after study, this design offers the advantage of providing a control group that enables more thorough assessment of the impact of a repeated intervention at a health care facility.

Moreover, in addition to the overall effect, the effect of each of the 5 interventions can be assessed. It nonetheless requires the event measured to be sufficiently frequent during each alternating period.

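### The overall programme effect rests only on an uncontrolled phase 2 vs phase 0 contrast about 22 months apart; the five On/Off blocks are never combined as a check on drift

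*Protocol article*

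**What the plan says.** The Objective section puts the programme first: "The study aims to assess the impact of a violence prevention program". The Data analysis section then names two primary analyses.

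- **Phase 1.** Average rates are compared "between the On and Off periods of each intervention (primary analysis"), with a separate chi-square test for each of the five blocks.
- **Phase 0 and phase 2.** The proportion of patients committing violence is "to be compared before and after implementation the overall prevention program (primary analysis"), by standard tests and then by mixed models with confounders. The mixed models are described for this contrast only.

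No pooled, summed or joint model across the five blocks is described. Yet the Discussion of study design presents the alternating control months as an advantage over a simple before/after study, and adds: "Moreover, in addition to the overall effect, the effect of each of the 5 interventions can be assessed".

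Under Study design, each component has two On and two Off months and then stays on permanently. The Off months of blocks B to E therefore already contain the earlier components.

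**The concern.** The question in the objective is answered by the one comparison that lacks the design's main protection. Between the midpoints of phase 0 and phase 2 lie about 22 months. Any trend over that time is fully confounded with the programme, and adjustment for measured patient factors does not remove it. A trend is plausible: events are reported by unblinded staff, reporting follows an awareness campaign of about six months, and reporting habits may fade or sharpen.

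Inside each block, On and Off months lie about one month apart on average, so drift does far less harm there. If the blocks are only tested singly, the trial could end with several inconclusive steps and an overall result that cannot be separated from a trend, although the data for a controlled check have been collected.

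**Working it through.** **Inputs from the article.** Sample size section: "A risk alpha of 5% and the statistical power of 80"%, a start rate of 20%, steps of 2.5 points (20% to 17.5%, and so on to 10% to 7.5%), and "The independence of the 5 interventions". Time frame: 37,820 patients in 20 months, so 37,820/20 = 1,891 a month and 3,782 per arm per block; about 3,780 in each of phases 0 and 2.

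**Assumptions not in the article.** A between-month SD τ of 0.5, 1.0, 1.5 or 2.0 points; strict monthly alternation within blocks; linear drift where stated.

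**1. The plan's own figure.** With A = [1.96√(2p̄(1−p̄)) + 0.8416√(p₁(1−p₁)+p₂(1−p₂))]² and n per arm = A[1+√(1+4d/A)]²/(4d²), block A gives A = 2.391 and n = 3,905, so 7,810 in total (Table 2: 7,802). The five blocks give 7,810 + 6,994 + 6,114 + 5,172 + 4,168 = 30,258 against the stated 30,224. The plan's figure reproduces, two-sided. At 3,782 per arm, patient-level power is 79.6%, 83.8%, 88.4%, 93.1% and 97.1% for A to E.

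**2. Drift.** A drift of δ points a month biases phase 2 vs phase 0 by 22δ. Without a trend term, it biases the sum of five block differences by 5 × 1 × δ.

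| δ (points/month) | Phase 2 vs phase 0 | Sum of blocks |
|---|---|---|
| 0.1 | 2.2 | 0.5 |
| 0.2 | 4.4 | 1.0 |
| 0.5 | 11 | 2.5 |

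A linear trend term in the phase 1 model removes the linear part of the last column.

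**3. One block at month level.** The variance of a monthly rate is v = τ² + mean p(1−p)/1,891. The binomial parts for A to E are 0.805, 0.719, 0.626, 0.527 and 0.421 squared points, sum 3.10. Block SE = √(v(1/2+1/2)) = √v. Example, block A at τ = 1.0: √1.805 = 1.34 points. Power uses the non-central t with 2 df.

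**4. Five blocks combined.** SE of the sum = √(5τ² + 3.10); SE of the average step = that/5. Under strict alternation a linear trend cuts the On/Off information from 5.0 to 4.0, so both SEs rise by √1.25, or 12%. With five block terms, one On effect and a trend, 20 − 7 = 13 df. With five On effects, 20 − 11 = 9 df.

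| τ | One block, power (2 df) | Average step, SE without trend | SE with trend | Power with trend (13 df) |
|---|---|---|---|---|
| 0.5 | 29-40% | 0.42 | 0.47 | above 99% |
| 1.0 | 20-23% | 0.57 | 0.64 | 95% |
| 1.5 | 14-15% | 0.76 | 0.85 | 78% |
| 2.0 | 11% | 0.96 | 1.07 | 58% |

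**5. Programme scale (planned effect 5 × 2.5 = 12.5 points).** At τ = 1.0 the sum has SE √8.10 = 2.85 points, or 2.85 × 1.118 = 3.2 with trend. Phase 2 vs phase 0 has variance τ²(1/2+1/2) + (0.2×0.8 + 0.075×0.925)/3,780 = 1.00 + 0.61 squared points, so SE 1.27. With binomial variance only, the SEs are √3.10 = 1.76 and √0.61 = 0.78.

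**The case against.** Four fair points can be made on the other side.

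- **The phase 1 data are used.** A reader might infer that the On/Off data are wasted. They are not: all 20 months feed five tests that are themselves labelled primary. Only their combination is absent.
- **Ten On against ten Off months is not the programme effect.** It is tempting to read it so. Because earlier components stay on, it estimates the average gain from adding one component (2.5 points planned), not the 12.5 points of the programme. A programme figure from phase 1 has to be the sum of the block effects.
- **The sum is not the more precise estimate.** Without a trend its SE is about 2.2 times that of phase 2 vs phase 0 (2.85/1.27). It also relies on the stated independence and absence of residual effect, and on no later fading of a component. Phase 2 observes the full programme directly.
- **The article is condensed.** A joint model might sit in a full analysis plan.

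The first three stand and limit what the fix may claim. The fourth stands only in part: the article does more than leave a detail open. It assigns the overall effect to the before/after contrast, labels that primary, and describes its mixed models for that contrast alone.

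**Conclusion.** The concern holds in a limited form. The programme effect is defined only by a contrast without concurrent control, open to 2.2 to 11 points of bias under assumed drifts of 0.1 to 0.5 points a month, against a planned 12.5. The five controlled blocks are never brought together to check it. A combined phase 1 analysis is a cheap improvement; its gain is protection against drift, not precision.

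The power figures depend on a between-month SD that the article does not give. A reader might conclude that no single block has useful power. The article does not support that: the low figures belong to a month-level test with an assumed SD, while the planned patient-level test has about 80% to 97%. Nor is the combined analysis safe at every SD, since its power is 58% at 2.0 points.

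**What to change.** Add to the Data analysis section a prespecified model on the 20 months of phase 1, with block (A to E) as fixed effect, a calendar trend and a random month effect, fitted in two forms:

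1. **One common On effect (13 df)**, reported as the average effect of adding one component.
2. **Block-specific On effects (9 df)**, reporting their sum with its interval as a drift-protected programme estimate beside phase 2 vs phase 0, plus a test of whether the block effects differ.

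State that the sum rests on independence and no residual effect, and that a clear disagreement with phase 2 vs phase 0 would point to drift or to failure of those assumptions.

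The cost is a paragraph of text and one model, in two forms, in software that the article already names; no extra data are needed. The Trial status section says that no outcome data had been processed, so at that point it could still be prespecified. The drawbacks are that the average does not show which component works and that the sum will have a wide interval: at an SD of 1.0 point, 2.26 × 3.2 = 7.2 points either side with 9 df.
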